**5.6 Study Procedures:**

In this randomized controlled study participants will be randomly assigned to either a control or an intervention group in a 1:2 ratio. While only the intervention group will have access to mHealth Fit After Baby program and personalized coaching from Lifestyle Coach during the 12-month study period, both control and intervention groups will receive the following:

1. Three assessment visits, conducted at the UCH CTRC. These visits will include the criteria and procedures listed in Table 3 below.

2. Study visit reminder calls 1 week before baseline, 6 months postpartum, 12 months postpartum.

3. A $200 stipend for completing all study visits. This stipend will help cover childcare and transportation costs. The payment is structured as follows: $50 following completion of the 6 week & 6 month visits, $100 following completion of the 12 month visit. Participants will also be given a small gift (<$5 value) at delivery (baby socks) from the study staff for participating in the study, and receive small gifts (<$5) (picture frame or book) by at the 6 month visit and by mail at 9 months, to remind patients about the study. Participants in the Fit After Baby group will have the opportunity to earn $5, $10, $15, and $20 gift cards (total up to $50) as an incentive to complete tasks within the mobile application.

During the COVID-19 pandemic, a COVID-19 lifestyle questionnaire, Edinburgh post-partum depression scale, and pregnancy physical activity questionnaire will be sent via email to all participants to assess the effect of social distancing on physical and mental health. Participants with and Edinburgh score >11 and/or suicidal ideation will be contacted by the PI for follow-up. This questionnaire will take 45 minutes to complete and will be completed using RedCap. It will be sent to participants in May, 2020. A reminder to complete the questionnaire will be sent 2 times, if they have not completed it within 1 week. Participants who complete the questionnaire will be compensated with a $20 Target Gift Card.

a. Study visits and parameters to be measured

Medical Record Review/Diagnosis Confirmation

Upon signing the consent form and enrolling in this research study, all women will be scheduled for their first of 3 study visits approximately 6 weeks postpartum. The consent form will include language to allow study staff access to the medical record information to confirm medical diagnoses by the inclusion criteria stated above. Subjects who do not have medical conditions as defined by the inclusion criteria stated above documented in their medical records will not be eligible to continue in the study. If a subject becomes pregnant during the course of the study, she will be asked to be followed during the pregnancy to determine occurrence of pregnancy complications and gestational weight gain.

Study Visits

At study visits, all women will be assessed for clinical outcomes, behavioral outcomes, mediating variables, and moderating variables (see table 3). Clinically relevant labs (pregnancy tests, OGTT, fasting glucose, HbA1c, TSH, LDL, triglycerides) will be reviewed when results are available. All subjects will complete approximately 45 minutes of questionnaires at study visits.

In accordance with ADA recommendations and UCH standard of care guidelines for postpartum diabetes screening for patients with prior GDM, which suggest 6 week postpartum glycemic status check via oral glucose tolerance test (OGTT), all enrolled subjects with a history of GDM will be offered an OGTT. Study staff will schedule this visit and with the subject’s permission, share OGTT results with subject’s pregnancy care provider (MD or CNM), thereby eliminating the scheduling of duplicate lab appointments. We anticipate this collaboration with OB caregivers will be welcomed, as published data demonstrate clinicians have a difficult time getting these women in for their 6 week postpartum OGTT – less than 50% of women had a 6 week postpartum OGTT.^[[42]](#endnote-42)^

All subjects will be instructed to arrive fasting to study visits, i.e. nothing except water for 10 hours prior to study visit. At study visits up to 50 cc of blood will be drawn, including fasting bloods and optional blood for storage.

During the first study visit, all enrolled subjects will be randomized using previously described permuted block scheme to either control or intervention arm.

Control arm: Subjects who enter the control arm will be shown how to sign up for the free Text4Baby program. Women assigned to the Text4Baby control arm will receive 2-4 free text messages per week from the Text4Baby program,^[[43]](#endnote-43)^ a nonprofit maternal child health program which provides information including baby care and resources for women tailored to their number of weeks postpartum. Since Text4Baby does not emphasize weight loss it will serve as an active control. If women are already enrolled they will be asked to continue to receive texts from the program.

Fit After Baby arm: Women assigned to the Fit After Baby program will use the app (see Table 1 for description of app components), as well as communicate with a lifestyle coach by email or phone. They will receive daily content for 12 weeks, and then less intensive interactions once per week plus home page tracking options until 12 months postpartum. Subjects randomized to the Fit After Baby arm will be shown how to download the app onto their phone. They will also be given a Fitbit and a body weight scale at the 6 week/baseline study visit and shown how to use these.

**Components:**

1) *Fit After Baby* mobile application: The *Fit After Baby* application is an evidence-based lifestyle intervention mobile app currently available for wireless devices running the iOS platform. The *Fit After Baby* program is adapted from the Diabetes Prevention Program^[[44]](#endnote-44)^ and tailored for this postpartum population at elevated cardiometabolic risk and for delivery via mobile app. The 12-week program contains weekly themes:

1) Introduction to the *Fit After Baby* program,

2) Self-monitoring and Energy Balance

3) Physical Activity

4) Stress Management

5) Carbohydrates

6) Fat

7) Protein

8) Portion Control when Eating Out and Eating In

9) Your FAB Environment

10) Staying on Track

11) Keep Up Your Physical Activity

12) Staying Motivated

Each day of the week contains one or more pages of content, and other components include goal-setting, quizzes, and games. There is a mechanism to communicate with the lifestyle coach by email or by text. Once participants receive their Fitbits, their physical activity data will be passively transmitted through wireless/Bluetooth connections (steps, distance, sleep, and calories burned). Participants will manually input their weights and set other goals using the app. They will use the free Fitbit application, linked to the *Fit After Baby* app, to track diet and exercise. Through the *Fit After Baby* application, users will receive real-time feedback on progress towards their weight loss, diet, and physical activity goals. If a participant elects not to do tracking via Fitbit, they will still be able to use the Fit After Baby application. Data from passive (manually inputted) and active tracking will be exported to datasheets and analyzed to assess participants’ adherence to the program, including manually inputted weights, days with physical activity data, transmitted by wearing Fitbit (provided) and/or logging physical activity, and days with dietary intake logged. Given that the app includes an option to manually enter physical activity, the use of Fitbit is not essential to the overall operation of the app and the program.

2) Lifestyle CoachA registered dietitian (RD) with training in patient-centered counseling techniques will work with the participants to help them set and achieve goals. The lifestyle coach will provide feedback, advice, and support through the *Fit After Baby* app, and via text messages and email messages. She will prepare to answer questions related to content for each week, how to use the app, and be available to answer any other questions the participant may want answered.

A study physician trained in patient centered counseling will periodically review email and text interactions, as well as notes from phone calls, to ensure adherence to these techniques. The coach and study physician will view progress of participants through a dedicated portal via an android coaching app where they can track diet, physical activity, weight, and progress towards individualized goals.

After a subject has completed the 12 month visit, we will send results of fasting glucose, lipid profile, hsCRP, HbA1c, and TSH from all study visits. The results will be accompanied by a letter from the study physician.

For women who completed their 6-week visit but do not complete their 6 or 12 month visits, we will attempt to reach them by phone, text, email, and/or mail. Additionally, during the consent process, we will get permission from subjects to contact a family member or friend if we are having trouble getting in touch with the subject at any point in the study.

Study Outcomes:

The primary outcomes are change in weight from baseline to 6 months and to 1 year postpartum (exit study visit), and change in weight from self-reported pre-pregnancy weight to one year postpartum.

Secondary outcomes**:** We will assess engagement and satisfaction with the program as potential mediators, defined as use of the app, adherence to self-monitoring of weight, diet, and physical activity, and interactions with the lifestyle coach. To assess changes in cardiometabolic risk factors we will obtain: blood pressure, waist circumference, and biomarkers at baseline, 6 months, and 12 months. We recognize that some of these measurements will be elevated in the postpartum state, however we hypothesize that we will see a greater change among women randomized to the intervention program. We will also assess sleep adequacy and appetite using scales embedded in the app and also sleep data from the Fitbit.

Recruitment targets and power calculation: We plan to recruit at least 7 participants per month, with a goal of consenting 140 subjects to account for recruitment yield of 50-70%. After 2 years we should have data from 81 participants at one year postpartum. With 54 subjects in the intervention group and 27 subjects in the control group, a 2-sample t-test controlling for baseline weight will have at least 87% power to detect a 4.2 kg difference between groups in 12 month weight change (the 4.2 kg difference with a pooled standard deviation of 5.7 kg was observed in the Balance after Baby RCT). This is adequate power for a pilot study designed to establish the foundation for a subsequent larger pragmatic trial of the *Fit After Baby* program.

+Structured interviews

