**5.4: Eligibility:**

Inclusion Criteria:

1. Age 18-45
2. Postpartum Body Mass Index (BMI): 26-45 kg/m^2^ (≥24 for Asians)

3) Positive history of one or more of the following complications in most recent singleton pregnancy:

- 1. Gestational diabetes mellitus (by Carpenter-Coustan criteria, IADPSG criteria, or a documented clinical diagnosis). Women with a glucose value >200 mg/dL after a 50-g glucose challenge test at >12 weeks gestation will also be included.
  2. Preeclampsia (high blood pressure and proteinuria diagnosed after 20 weeks gestation)
  3. Gestational hypertension (new hypertension diagnosed after 20 weeks without proteinuria)
  4. Pre-term delivery (32-37 weeks)
  5. Small for gestational age (<10th percentile for gestational age)

4) Access to and be willing to use a wi-fi enabled iPhone (5 or higher) or iPod (5 or higher).

5) Capable of providing informed consent

6) Between 4 weeks and 16 weeks after delivery

Exclusion criteria include:

1. Personal history of Type 1 or 2 diabetes
2. Personal history of breast cancer or any other type of cancer other than a basal cell skin cancer;
3. Personal history of major chronic illness all to be assessed by the study physician for ability to participate, including cardiovascular disease (coronary artery disease, congestive heart failure, valvular heart disease, stroke, transient ischemic attack, or intermittent claudication), kidney disease affecting kidney function severe enough to affect participation, liver disease affecting liver function severely enough to affect participation, venous or arterial thromboembolic disease, untreated adrenal insufficiency, depression requiring hospitalization within the past 6 months, or non-pregnancy related illness requiring overnight hospitalization in the past 6 months;
4. Underlying disease/treatment that might interfere with participation in/completion of the study (e.g. significant gastrointestinal conditions, major psychiatric disorders affecting the ability to participate, and others at the discretion of the study clinician);
5. Re-current pregnancy;
6. Pregnancy of twins or multiples;
7. Diagnosis of diseases associated with glucose metabolism;
8. Current or planned participation in a commercial weight loss program (i.e. Jenny Craig) over the duration of the study;
9. Previous or planned bariatric surgery;

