*NOTE: Measures will be taken to review subject data and diagnose diabetes according to American Diabetes Association (ADA) guidelines. The following values at the specified timepoints throughout the study year indicate that the subject will need to repeat the abnormal test to confirm the diagnosis of diabetes:

• At the 6-week visit, if the subject has a fasting glucose value >126 or a 2-hour OGTT glucose value >200. The HbA1c value collected at the 6-week visit is exploratory and is not clinically used to diagnose diabetes at 6-weeks, given that the result will be affected by hyperglycemia during pregnancy.

• At the 6-month and 12-month visits, if the subject has a fasting glucose value > 126 or a 2-hour OGTT glucose value >200 or if the HbA1c value is >7.0. For HbA1C values between 6.5 and 7.0, we will use the values from the OGTT as the standard for making a diagnosis for DM.

If two of the subject’s initial clinical tests exceed these values, they will be diagnosed with diabetes at that timepoint. If one of the subject’s initial clinical tests exceeds these values we will schedule a repeat fasting glucose, OGTT, or HbA1c. If the subject’s repeat test result exceeds these values, the subject will be diagnosed with diabetes. Subjects diagnosed with diabetes at the 6 week visit will be excluded from the study. If a subject is diagnosed with diabetes at any visit other than the 6 week visit, we will continue to follow them. This is to ensure that we can collect data on all randomized subjects, including body weight which is the primary outcome of the study. We will assist all subjects diagnosed with diabetes with a referral to an appropriate provider to manage their condition.

Validated Questionnaires

1. Demographics Questionnaire (Based on the Behavioral Risk Factor Surveillance System (BRFSS). http://hmcrc.srph.tamhsc.edu/Measures/BRFSS%20Demographic.pdf

2. Social Support for Eating Habits Survey - Sallis. http://www-rohan.sdsu.edu/faculty/sallis/socialsupport-eatinghabits.pdf.

3. Social Support for Physical Activity - Sallis. http://www-rohan.sdsu.edu/faculty/sallis/socialsupport-exercise.pdf.

4. Self Efficacy Survey for Diet and Exercise Behaviors. http://www-rohan.sdsu.edu/faculty/sallis/self-efficacy-coverandexercise.pdf

5. Perceived Stress Scale. http://www.macses.ucsf.edu/Research/Psychosocial/notebook/PSS10.html.

6. Edinburgh Post-Partum Depression Scale (EPDS)* http://www.fresno.ucsf.edu/pediatrics/downloads/edinburghscale.pdf.

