**Statistical Analysis**: The analysis for the primary outcomes will be intent-to-treat, using longitudinal mixed methods to account for loss to follow-up and censored participants. Due to the longitudinal nature of this study, we will assess the change in weight from the 6-week study visit to weight at 6 and 12 months by a mixed model analysis with an exchangeable correlation structure and adjustment for weight gain during pregnancy, and breastfeeding (a mediating effect). Within this model, we can further assess differences in weight between various time points by contrasts. We will also compare the delta weight prepregnancy to 6 and 12 months postpartum in the intervention group to the control group using a multivariate regression model, adjusting for age and race. Secondary clinical outcomes will be compared between groups by a generalized linear mixed model analysis, similar to the primary outcome analysis. When necessary, adjustment for multiple comparisons will be made. We will assess reach, effectiveness, and adoption per the RE-AIM model to prepare for a pragmatic trial (Table 2). We will use content-based analysis on focus group data to assess perceived barriers and facilitators to success of the intervention.

**Anticipated results**: Primary outcome: We expect that women who participate in the *Fit After Baby* program will demonstrate increased weight loss in the postpartum year vs. the Text4Baby control group. Secondary outcomes**:** We expect an improvement in cardiometabolic risk factors among women randomized to the Fit After Baby program. We anticipate that increased engagement and satisfaction will be associated with increased weight loss. We expect that decreased caloric intake relative to expenditure and increased physical activity will help to mediate weight loss. We anticipate that postpartum depression may interfere with weight loss as it will decrease engagement with the program, and appetite and sleep may also moderate weight loss.

| **Table 2: Relevant RE-AIM Outcomes** | **Measures/Data Source** | |
| --- | --- | --- |
| **REACH** | | |
| 1) Proportion of approached women agreeing to participate  2) Proportion of recruited women initiating program | | 1) Recruitment data  2) App usage data |
| **EFFECTIVENESS** | | |

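### The model for the blood pressure and glycaemic secondary outcomes leaves out the index pregnancy complication, which costs some precision but causes no bias

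*Protocol*

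**What the plan says.** Section 5.6 of the protocol, under Study Outcomes, lists as secondary outcomes "blood pressure, waist circumference, and biomarkers at baseline, 6 months, and 12 months". Without naming which measures it means, it then adds "We recognize that some of these measurements will be elevated in the postpartum state, however we hypothesize that we will see a greater change among" those in the intervention arm. The notes to Table 3 set the 6-week HbA1c aside for diagnosing diabetes, "given that the result will be affected by hyperglycemia during pregnancy". The outcomes-monitoring text repeats this in the paragraph on women with recent gestational diabetes. Table 3 nevertheless lists that HbA1c among the clinical outcomes at Visit 1.

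Section 5.4 requires "Positive history of one or more of the following complications in most recent singleton pregnancy". The list is gestational diabetes, preeclampsia, gestational hypertension, preterm delivery and small-for-gestational-age birth. Two of the five are hypertensive disorders, for example "Gestational hypertension (new hypertension diagnosed after 20 weeks without proteinuria").

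Section 5.5 describes permuted blocks of varying size in a 2:1 ratio and mentions no stratification factor. The Statistical Analysis text states: "Secondary clinical outcomes will be compared between groups by a generalized linear mixed model analysis, similar to the primary outcome analysis". The model it refers to has "adjustment for weight gain during pregnancy, and breastfeeding (a mediating effect"). Age and race enter only the separate regression on pre-pregnancy weight. Complication type appears in no model.

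**The concern.** Change is measured from a point at which some women are still recovering from the pregnancy. On the entry definitions, how much there is to recover probably depends on the complication: glycaemia after gestational diabetes, blood pressure after a hypertensive disorder. Recovery shared by all women has the same expectation in both arms and cancels. Recovery that differs by complication cancels only on average. In any one trial it adds unexplained variation, and an uneven split of complications between arms moves the estimate one way or the other.

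The rationale in section 5.1 is to give preliminary data for a larger trial that will assess weight loss and risk factors. Less precise risk-factor estimates serve that purpose less well, and the variable that would sharpen them is already confirmed from medical records at entry.

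**Working it through.** **The plan's own figure.** The only power statement concerns 12-month weight change: 54 against 27, 4.2 kg, SD 5.7 kg. The standard error is 5.7 × √(1/54 + 1/27) = 1.34 kg. A noncentral t with 79 df at two-sided 0.05 (assumed, since alpha is not stated) gives 87.0%, which agrees with the stated figure of at least 87%. There is no such figure for blood pressure or glycaemia.

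**Inputs.** The arm sizes are the protocol's. The share with the complication (40%), the extra recovery d (4, 8 or 12 mmHg) and the SD of change within complication groups (10 mmHg) are assumptions.

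**Chance imbalance.** The SD of the between-arm difference in share is √(0.4 × 0.6 × (1/54 + 1/27)) = 0.115, or 11.5 percentage points. A difference of 20 points or more occurs in about 8% of trials. For shares of 20 to 50% the SD is 9.4 to 11.8 points. A 20-point imbalance shifts the estimate by 0.20 × d = 0.8, 1.6 or 2.4 mmHg.

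**Precision, change-score model.** Variance inflation from leaving the complication out is 1 + 0.24 × d²/100.

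| d (mmHg) | Variance | Standard error | Equivalent sample loss |
|---|---|---|---|
| 4 | +3.8% | +1.9% | 3.7% |
| 8 | +15.4% | +7.4% | 13.3% |
| 12 | +34.6% | +16.0% | 25.7% |

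In SD units, for any outcome and shares of 30 to 50%, the standard error rises by 2.6 to 3.1% for a recovery gap of 0.5 SD and by 10.0 to 11.8% for a gap of 1 SD.

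**Precision, with the baseline value as covariate.** Assume the complication raises only the baseline value. A within-visit variance of 100 and a correlation of 0.5 between visits give the same SD of change of 10. The residual variance without the indicator is 100 − 50²/(100 + 0.24d²); with it, 100 − 50²/100 = 75. For d = 4, 8 and 12 the first is 75.9, 78.3 and 81.4, so the standard error rises by 0.6%, 2.2% and 4.2%. With a correlation of 0.6 and the same SD of change, the rises are 0.8%, 3.0% and 5.9%.

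**Net of degrees of freedom.** I simulated 8,000 trials per setting with two indicators in the model, only one of them informative. The omission then costs 0.6%, about 6% and about 14.5% in the change-score model. With baseline adjustment it costs nothing at d = 4 (a gain of 0.5 to 0.7%), 0.9 to 1.8% at d = 8 and 2.9 to 4.6% at d = 12. If recovery does not differ at all, the two indicators raise the mean standard error by 1.3% (2.347 to 2.377 in the change-score model); 1.5% is a round allowance.

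**Validity.** In 20,000 simulated trials per setting without adjustment, type I error was 5.0 to 5.1% and the mean estimate was about zero.

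**The case against.** The strongest reply is that the covariate list for secondary outcomes is commonly left to a statistical analysis plan, which is not shown, and that a model described as similar to another is not a closed list. This stands in part: it cannot be said that the trial will ignore the complication. But the protocol does name the model to follow and its covariates, and those are the ones a reader would carry over.

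Several stronger readings are tempting, and the documents do not support them.

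- *Imbalance produces a false programme effect.* The control arm is concurrent and randomised, so there is no bias and the nominal error rate holds. At d = 8 the unadjusted standard error is √115.36 × √(1/54 + 1/27) = 2.53 mmHg. The 1.6 mmHg shift from a 20-point imbalance is 0.6 of that, and the ordinary confidence interval already allows for it.
- *The protocol says baseline blood pressure and glucose are shifted.* Only HbA1c is named. Blood pressure is an inference from the hypertensive entry criteria. The protocol uses the 6-week fasting glucose, and the glucose tolerance test where done, to diagnose diabetes, so it treats 6-week glucose as usable.
- *Antihypertensive use goes unrecorded and treated women's values should be removed.* A Medical History Update is scheduled at all three visits and the form is not shown. Removing those values would also condition on treatment that may follow randomisation.

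It is also true that the size of any recovery gap is nowhere in the documents, and that much of the loss disappears if the baseline value is a covariate.

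**Conclusion.** The point holds as a minor one about precision. As described, neither the randomisation nor the secondary model uses complication type, although the protocol concedes that at least the 6-week HbA1c carries over from pregnancy and recruits women with and without the relevant disorders. On the assumptions above, the omission costs about 2 to 16% in standard error for a change-score analysis and about 0 to 5% with baseline adjustment. At d = 8 in the change-score model, the 95% half-width is about 5.0 rather than 4.7 mmHg.

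These sizes depend on an assumed share, recovery gap, SD and between-visit correlation. If recovery differs little between complications, there is nothing to gain. The primary weight outcomes and the stated power are not affected.

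**What to change.** For the blood pressure and glycaemic secondary outcomes only, prespecify before unblinded analysis that the model adjusts for:

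- the baseline value of the outcome;
- an indicator of index gestational diabetes;
- an indicator of index hypertensive disorder (preeclampsia or gestational hypertension).

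If the baseline visit is modelled as a response rather than a covariate, give each indicator an interaction with visit. A main effect alone captures a constant difference in level, not a different course over time. There is no need to extend this to waist circumference, lipids or hsCRP, for which no complication-specific recovery is argued.

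The cost is one sentence in the analysis section and a few degrees of freedom: about a 1.5% larger standard error if recovery does not differ. No new data are needed, because baseline values are taken at Visit 1 and complications are confirmed from medical records. I would not add a sensitivity analysis that removes treated women's values.
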